# The TANGO-DM randomized controlled trial study protocol: treatment outcomes for gestational diabetes diagnosed according to WHO 2013 or WHO 1999 thresholds

**DOI:** 10.1186/s12884-025-07230-x

**Published:** 2025-02-17

**Keywords:** Gestational diabetes mellitus, WHO 1999, IADPSG, Randomized controlled trial, Large-for-gestational-age

## Abstract

**Introduction:**

Gestational diabetes mellitus (GDM), or hyperglycemia first diagnosed in pregnancy, affects 7–10% of all pregnancies worldwide. Perinatal risk rises with increasing glycemia at oral glucose tolerance test (OGTT). The new (2013) WHO criteria recommend a lower fasting, and a higher post-load threshold for GDM diagnosis in comparison to the old (1999) WHO criteria. To date, however, outcomes of GDM treatment for those affected by the altered diagnostic criteria, has not been well investigated. We hypothesized that intensive GDM treatment according to the new (2013) GDM criteria would result in a reduction in infants with birth weight > 90th centile (large for gestational age, LGA), in comparison to treatment according to the old criteria (1999).

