**Methods:**

The TANGO-DM trial is an open label, multicenter randomized controlled trial. Participants are pregnant with a gestational age between 16 + 0 and 32 + 0 weeks, who underwent a 1-step venous 2- or 3-point 75-gram oral OGTT, were eligible if they had glucose concentrations discordant between the old (1999) and the new (2013) criteria. After informed consent, women are randomized to either intensive GDM treatment, consisting of dietary advice and glucose monitoring and, if euglycemia is not reached, antihyperglycemic agents, or normal obstetric care without GDM treatment. The primary outcome is large-for-gestational-age infants (birth weight > 90th percentile). Secondary outcome measures include maternal complications, obstetric complications, neonatal complications, obstetric interventions, quality of life, and healthcare and societal costs. Outcomes will be analyzed according to the intention-to-treat principle. The study is powered to detect a reduction in LGA from 16% in the untreated to 10% in the treated group, which requires 1032 participants (516 per arm; alpha-error 5% for 80% power).

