Based on the 2013 WHO thresholds, an additional group of pregnant women with mild hyperglycemia, formerly labeled as normal glucose tolerance, are now classified as having GDM and will be advised treatment. As a result of adding the 1-hour value, there is a group of women who would not have been diagnosed because the 1-hour blood draw did not exist in the WHO 1999 guideline. In addition, there is a group of women formerly labeled as having GDM who are now classified as normal glucose tolerance. Hillier et al. showed that expanded criteria for GDM might almost double the incidence of GDM without lowering risk in adverse pregnancy outcome [12]. The recent GEMS trial showed similar results in a large group of women who were randomized with the use of lower or higher glycemic criteria for diagnosis. However, on closer examination of the GEMS subgroup analyses among participants with OGTT results discordant between the higher and lower criteria, allocation to intensive GDM treatment was found to lead to a large reduction in large for gestational age infants. The fact that the GEMS trial was not designed to investigate this discordant group hampers interpretation of this particular finding, which may be of relevance to individual patients [13]. Therefore, to date, there is no evidence from well-designed randomized trials, that treatment of GDM diagnosed by the new (2013) WHO criteria, but not by the old (1999) criteria, leads to improved perinatal and maternal outcomes. Thus, benefits and harms, and cost-effectiveness of adopting these new criteria are currently unknown [14–16].

The new (2013) WHO criteria have now been implemented in many, but not all, countries [17, 18]. The Netherlands, along with other European countries including the United Kingdom, Sweden, Denmark and Belgium, had, up until the start of this study (2018), not implemented the WHO 2013 criteria [19]. Since then, Sweden has implemented the WHO 2013 criteria, and Belgium has introduced a two-step method, in which at the second test the diagnosis is made with the WHO 2013 criteria.

There is thus an immediate and short-lived window of opportunity to assess the potential health benefits and economic costs of the WHO 2013 criteria.

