**Fig. 1 Fig1:**
[figure not shown]
Consort flow diagram

Women are eligible if they have a singleton pregnancy, with a gestational age between 16 + 0 and 32 + 0 weeks at study entry, aged *≥* 18 years, without pre-conceptional diabetes, a major fetal congenital abnormality, or significant medical or psychiatric co-morbidities as judged by the investigator (e.g., high dose corticosteroid treatment), with the ability to understand the informed consent form. In addition, participants will need to have undergone a 2- or 3-point 75-gram OGTT, consisting of a fasting, 1 h (in case of 3-point OGTT) and 2 h post load glucose concentration via venipuncture, conducted between gestational ages 16 + 0 and 30 + 0 weeks yielding glucose concentrations discordant between the old WHO (1999) and the new WHO (2013) criteria.

A discordant result is defined as any single blood glucose concentration during a 75-gram venous blood OGTT within the following ranges, in the absence of any other glucose concentration exceeding the upper limit of discordancy (Table 1). For example, a pregnant individual is eligible if she has a fasting glucose between 5.1 mmol/l and 7.0 mmol/l, as long as the 2-hour glucose is below 8.5 mmol/l. Similarly, a pregnant individual with a 2-hour glucose between 7.8 mmol/l and 8.5 mmol/l is eligible, as long as the fasting glucose is < 7.0 mmol/l.

**Table 1 Tab1:** Glucose cut of values

	WHO 2013	WHO 1999
Fasting glucose	≥ 5.1 mmol/l	< 7.0 mmol/l
1-hour glucose	≥ 10 mmol/l	
2-hour glucose	< 8.5 mmol/l	≥ 7.8 mmol/l

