#### Planned analyses

Baseline characteristics will be presented as frequencies and percentages in each group, or as averages (mean or median) with standard deviations or interquartile ranges as appropriate. The primary outcome will be evaluated by estimating the relative risk between both treatment arms. Analyses will be conducted in both the intention-to-treat and per protocol population for the primary outcome.

Relative risks will be estimated for categorical outcomes, with 95% confidence intervals, and χ2 tests for significance. Fisher’s exact test will be used for sparse events where assumptions of the χ2 test are not met. Continuous data will be described as means with standard deviation if normally distributed, or medians with interquartile ranges when not normally distributed; tests for significance are t-tests or Mann-Whitney U tests, respectively. The Hodges-Lehman estimator will be used to calculate the confidence interval for the difference in medians.

Individuals who were randomized to normal obstetric care but for unknown reasons received treatment they will be excluded from the per protocol analysis. If the treatment followed an abnormal repeat OGTT they will remain in the per protocol analysis. Individuals who were randomized to GDM treatment but for unknown reasons never received treatment will be excluded from the per protocol analysis. If, per example, they did not receive treatment because of preterm birth they will remain in the per protocol analysis.

Subgroup analyses will be performed for BMI (under or above 30 kg/m2), early or late GDM (before or after 24 weeks) and according to the result of the OGTT (abnormal fasting result, abnormal postprandial result, or both).

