## Discussion

The TANGO-DM trial is the first to provide randomized evidence on the effectiveness and cost-effectiveness of intensive GDM treatment versus no treatment in a group of women that would formerly i.e. before the new (2013) WHO criteria would not have been diagnosed as GDM, and subsequently would not have received treatment. It will provide guidance for the justification of these new diagnostic criteria and the study results will have important clinical implications. Moreover, the cohort formed by participants of the TANGO-DM trial provides an opportunity to assess differences in long-term health outcomes mothers and their offspring after treatment of no treatment.

Strengths of this trial include the large sample size and randomized design. We will report on all core outcome measures defined for GDM studies and, next to the effectiveness manuscript, provide a cost-effectiveness analysis [29]. The study did not proceed as originally planned due to the impact of the complexities associated with managing a large, multidisciplinary trial. The study involved multiple disciplines, including gynecology, midwifery, internal medicine, and clinical chemistry, which added complexity to its execution.

A limitation of this study may be non-compliance with voluntary questionnaires sent during pregnancy and the postpartum period. Compliance to fill in the questionnaires will be enhanced by sending questionnaires per email that can be filled in online and are compatible with smartphone.

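### The pooled treated-versus-untreated relative risk answers the stated aim but not the new-versus-old-criteria hypothesis, and the planned OGTT subgroup separates the diagnostic types largely but not cleanly

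*Protocol article*

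**What the plan says.** All references are to the protocol article.

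- **Hypothesis (Abstract, Introduction):** "intensive GDM treatment according to the new (2013) GDM criteria would result in a reduction in infants with birth weight > 90th centile", "in comparison to treatment according to the old criteria (1999". This compares two diagnostic policies.
- **Randomised contrast (Abstract, Methods):** intensive GDM treatment "or normal obstetric care without GDM treatment". The aim under Aims, design and setting matches this: treatment against normal obstetric care in women with a discordant OGTT.
- **Eligibility (Participants and eligibility criteria, Table 1):** one route is a "fasting glucose between 5.1 mmol/l and 7.0 mmol/l, as long as the 2-hour glucose is below 8.5 mmol/l". By the other, "a pregnant individual with a 2-hour glucose between 7.8 mmol/l and 8.5 mmol/l is eligible", provided fasting glucose is under 7.0 mmol/l. A 1-hour value of 10 mmol/l or more also qualifies.
- **Both directions acknowledged (Introduction):** besides the newly diagnosed women, "there is a group of women formerly labeled as having GDM who are now classified as normal glucose tolerance".
- **Analysis (Planned analyses):** one relative risk between the arms for LGA, and a subgroup analysis "according to the result of the OGTT (abnormal fasting result, abnormal postprandial result, or both".
- **Population as later described (Discussion):** women who "would formerly i.e. before the new (2013) WHO criteria would not have been diagnosed as GDM".
- **Intended conclusion (Abstract, Discussion):** evidence for or against using the 2013 criteria.

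**The concern.** Treatment has opposite policy meanings in the two discordant types. In a 2013-only woman, the treated arm is managed as WHO 2013 implies and the untreated arm as WHO 1999 implies. In a 1999-only woman it is the reverse. If treatment helps 1999-only women, that is an argument against criteria that no longer diagnose them, yet it moves the pooled relative risk in the direction that the hypothesis calls success for the 2013 criteria.

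What is at stake is the conclusion, not the randomised comparison. A favourable pooled result could be cited for adopting WHO 2013 when part of it came from women whom WHO 2013 reclassifies as normal. The population sentence in the Discussion makes that reading easier, because it describes all participants as previously undiagnosed.

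**Working it through.** **1. The plan's own sample size.** Inputs (Sample size section and Abstract): LGA 16% versus 10%, alpha 5% (two-sided assumed), power 80%, 5% loss to follow-up. With unpooled variance:

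n = (0.16×0.84 + 0.10×0.90) × (1.960 + 0.842)² / 0.06² = 0.2244 × 7.849 / 0.0036 ≈ 489.3, so 490 per arm; 490 / 0.95 = 515.8, so 516 per arm.

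This reproduces 516 per arm (1032 in total). The sample size is not in dispute.

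**2. Who is enrolled, and where the planned subgroup puts them.** Every eligible pattern has fasting under 7.0 and 2-hour under 8.5 mmol/l.

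| Fasting | 1-hour | 2-hour | Criteria met | Planned subgroup |
|---|---|---|---|---|
| ≥5.1 | <10 or not measured | <7.8 | 2013 only | fasting |
| ≥5.1 | ≥10 | <7.8 | 2013 only | both |
| ≥5.1 | any or not measured | 7.8 to <8.5 | 2013 and 1999 | both |
| <5.1 | ≥10 | <7.8 | 2013 only | postprandial |
| <5.1 | ≥10 | 7.8 to <8.5 | 2013 and 1999 | postprandial |
| <5.1 | <10 | 7.8 to <8.5 | 1999 only | postprandial |
| <5.1 | not measured | 7.8 to <8.5 | 1999; 2013 status not fully known | postprandial |

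Three things follow.

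- The fasting stratum is purely 2013-only.
- On 3-point tests the postprandial stratum holds all three types, and the stratum for both abnormalities holds two.
- Women meeting both sets are admitted although eligibility is defined by discordance. For them the two sets do not disagree.

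**3. Pooled contrast against policy contrast.** Let a, b and c be the shares of 2013-only, 1999-only and both-criteria women (a + b + c = 1). Assume the planned 16% untreated and 10% treated in every type.

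- Pooled, treated versus untreated: 16% − 10% = 6.0 points for any mix.
- LGA if managed by WHO 2013: 0.10a + 0.16b + 0.10c.
- LGA if managed by WHO 1999: 0.16a + 0.10b + 0.10c.
- Difference: 6 × (a − b) points.

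| a / b / c (assumed) | Managed as 1999 | Managed as 2013 | Difference (points) | RR |
|---|---|---|---|---|
| 100 / 0 / 0% | 16.0% | 10.0% | 6.0 | 0.63 |
| 90 / 10 / 0% | 15.4% | 10.6% | 4.8 | 0.69 |
| 80 / 10 / 10% | 14.8% | 10.6% | 4.2 | 0.72 |
| 70 / 30 / 0% | 14.2% | 11.8% | 2.4 | 0.83 |

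**4. Precision if the criteria claim rests on 2013-only women.** Pooled-variance test, two-sided 5%, 16% versus 10%, 490 evaluable per arm: power = Φ[(0.06 − 1.96 √(2×0.13×0.87/n)) / √(0.2244/n)].

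- All women, n = 490: 79.8%.
- 80% share, n = 392: Φ[(0.06 − 0.0471)/0.0239] = 70.5%.
- 60% share, n = 294: Φ[(0.06 − 0.0544)/0.0276] = 58.1%.

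**The case against.** The strongest reply is that the operative aim, the randomisation and the analysis agree. Aims, design and setting asks about treatment versus normal care in women selected by a discordant OGTT, and the intention-to-treat relative risk answers exactly that. This stands. A reader might infer that the primary analysis is invalid, and the documents do not support that. The fault lies in the hypothesis and in the conclusions drawn.

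A reader might also infer that no planned subgroup separates the types. That goes too far. The fasting stratum isolates 2013-only women, and on 2-point tests the postprandial stratum isolates women positive by WHO 1999 and negative on every 2013 value measured. The mixing comes through the 1-hour value on 3-point tests. Exact category rules and interaction tests may sit in an analysis plan that is not shown. The categories that the article does fix, however, are defined by time point and not by criterion.

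Third, the protocol nowhere states a rule that a pooled benefit supports WHO 2013. This is also true. The Abstract's hypothesis and its promised conclusion invite that reading without stating it.

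Finally, the case mix is assumed. One could posit equal shares of 2013-only and 1999-only women, which makes the policy contrast zero. The protocol's Discussion expects a net increase of 3400 to 8500 affected pregnancies a year under the 2013 criteria, which points to more 2013-only than 1999-only women nationally. The enrolled mix could differ, but an even split should not be the headline.

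**Conclusion.** The concern holds in a limited form. The pooled relative risk is a sound answer to whether treatment helps the women enrolled. It does not, alone, test the hypothesis as worded or settle the case for WHO 2013, because benefit in 1999-only women adds to it while counting against those criteria. The Discussion's population statement is wrong for every participant with a 2-hour value of 7.8 to <8.5 mmol/l, since WHO 1999 diagnosed them.

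The size depends on a mix that the documents do not give. With a uniform 6-point effect and none meeting both sets, the policy contrast is 4.8 points at 10% and 2.4 points at 30% 1999-only women, against a pooled 6 points. If 1999-only and both-criteria women are rare, the gap is small, but nothing in the article caps their share. Under a uniform effect the pooled estimate also describes 2013-only women correctly. If effects differ by type, only type-specific estimates show it.

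This should be fixed. It does not undermine the trial.

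**What to change.** 1. Reword the hypothesis and primary conclusion as treatment versus no GDM treatment in the eligible women.
2. Define the OGTT subgroup by criterion met: 2013-only, 1999-only, both. Add an unclassifiable category only for 2-point tests with fasting <5.1 and 2-hour 7.8 to <8.5 mmol/l; every other eligible 2-point result can be classified. Test treatment by type.
3. Base any statement for or against WHO 2013 on the 2013-only estimate read together with the 1999-only estimate, not on the pooled result alone. A recoded comparison (2013-only treated plus 1999-only untreated, against the reverse, stratified by type) can be an optional supportive analysis. It should not be a condition for conclusions: its power at 490 evaluable per arm is about 61%, 39% and 20% with 10%, 20% and 30% 1999-only women and none meeting both.
4. Correct the population statement in the Discussion, and reconcile the eligibility ranges with the term discordant, given that they admit women who meet both sets.

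**Cost.** Only wording and pre-specification change. OGTT values are already collected (Baseline characteristics), and type is fixed before randomisation, so the within-type comparisons remain randomised, although randomisation is stratified by centre only. The downside is that the criteria claim rests on fewer women, with the reduced power shown in the working. The report should state this openly.

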**Methods:**

The TANGO-DM trial is an open label, multicenter randomized controlled trial. Participants are pregnant with a gestational age between 16 + 0 and 32 + 0 weeks, who underwent a 1-step venous 2- or 3-point 75-gram oral OGTT, were eligible if they had glucose concentrations discordant between the old (1999) and the new (2013) criteria. After informed consent, women are randomized to either intensive GDM treatment, consisting of dietary advice and glucose monitoring and, if euglycemia is not reached, antihyperglycemic agents, or normal obstetric care without GDM treatment. The primary outcome is large-for-gestational-age infants (birth weight > 90th percentile). Secondary outcome measures include maternal complications, obstetric complications, neonatal complications, obstetric interventions, quality of life, and healthcare and societal costs. Outcomes will be analyzed according to the intention-to-treat principle. The study is powered to detect a reduction in LGA from 16% in the untreated to 10% in the treated group, which requires 1032 participants (516 per arm; alpha-error 5% for 80% power).

**Discussion:**

The TANGO-DM trial will provide high-level evidence to support or refute the use of the new 2013 WHO diagnostic criteria in terms of their ability to lower the number of large for gestational age infants and/or improve maternal and perinatal outcomes and/or costs in women with gestational diabetes.

**Trial registration:**

Central Committee on Research Involving Human Subjects (CCMO) (NL63013.018.18). Registered on 22 September 2018.

**Supplementary Information:**

The online version contains supplementary material available at 10.1186/s12884-025-07230-x.

## Introduction

Gestational diabetes mellitus (GDM), or hyperglycemia first diagnosed in pregnancy, complicates approximately 7–10% of all pregnancies worldwide [1, 2]. GDM carries substantial maternal and perinatal risks, including large-for-gestational-age (LGA) neonates, shoulder dystocia, caesarean section, preeclampsia and neonatal hypoglycemia. Children born from pregnancies complicated by GDM have increased risks of obesity, diabetes and cardiovascular problems in later life [3, 4]. Treatment of GDM with a combination of dietary advice and, if necessary, glucose-lowering medication has been shown to decrease the incidence of some, but not all, adverse pregnancy outcomes, with some inconsistencies between studies [4, 5].

In 1999, the WHO released guidance for GDM diagnosis thresholds, which were informed primarily by the existing diagnostic guidelines for type 2 diabetes (DM2) [6, 7] In a large prospective international cohort, the Hyperglycemia and Adverse Pregnancy Outcomes (HAPO) study demonstrated a linear association between increasing maternal glucose concentrations at mid trimester oral glucose tolerance testing (OGTT) and increasing rates of LGA, neonatal hypoglycemia, caesarean section rate, and high cord serum C-peptide concentrations [8]. This association was also evident at glucose concentrations below the WHO 1999 threshold for GDM [8, 9]. Thus, in 2013, triggered by the HAPO findings, the WHO issued new diagnostic thresholds for GDM, based on the consensus that an increased odds ratio (1.75 compared to median glucose concentrations) for selected adverse pregnancy outcomes inferred that GDM treatment should be beneficial in an extended group [10]. Subsequently, most countries implemented these new diagnostic thresholds [1, 11].

Based on the 2013 WHO thresholds, an additional group of pregnant women with mild hyperglycemia, formerly labeled as normal glucose tolerance, are now classified as having GDM and will be advised treatment. As a result of adding the 1-hour value, there is a group of women who would not have been diagnosed because the 1-hour blood draw did not exist in the WHO 1999 guideline. In addition, there is a group of women formerly labeled as having GDM who are now classified as normal glucose tolerance. Hillier et al. showed that expanded criteria for GDM might almost double the incidence of GDM without lowering risk in adverse pregnancy outcome [12]. The recent GEMS trial showed similar results in a large group of women who were randomized with the use of lower or higher glycemic criteria for diagnosis. However, on closer examination of the GEMS subgroup analyses among participants with OGTT results discordant between the higher and lower criteria, allocation to intensive GDM treatment was found to lead to a large reduction in large for gestational age infants. The fact that the GEMS trial was not designed to investigate this discordant group hampers interpretation of this particular finding, which may be of relevance to individual patients [13]. Therefore, to date, there is no evidence from well-designed randomized trials, that treatment of GDM diagnosed by the new (2013) WHO criteria, but not by the old (1999) criteria, leads to improved perinatal and maternal outcomes. Thus, benefits and harms, and cost-effectiveness of adopting these new criteria are currently unknown [14–16].

The new (2013) WHO criteria have now been implemented in many, but not all, countries [17, 18]. The Netherlands, along with other European countries including the United Kingdom, Sweden, Denmark and Belgium, had, up until the start of this study (2018), not implemented the WHO 2013 criteria [19]. Since then, Sweden has implemented the WHO 2013 criteria, and Belgium has introduced a two-step method, in which at the second test the diagnosis is made with the WHO 2013 criteria.

There is thus an immediate and short-lived window of opportunity to assess the potential health benefits and economic costs of the WHO 2013 criteria.

